#### Intervention content and structure

In order to evaluate intervention acceptability, usefulness, participants´ learning, implementation, and transfer, the Questionnaire for Professional Training Evaluation (Q4TE), a validated training evaluation questionnaire [24] will be used. The questionnaire consists of six subscales (*Satisfaction, Utility, Knowledge, Application to practice, Individual organizational results, and Global organizational results*) with 12 items that can be rated on an 11-point response scale ranging from 0 percent = *completely disagree* (coded as 0) to 100% = *completely agree* (coded as 10). For item 11 (“Overall, it seems to me that the application of the training contents has facilitated the workflow in my company.”) the expression “my company” was changed to “my hospital unit” to more accurately represent the study setting. Previous research has shown that the Q4TE has good discriminant validity and internal consistency (Cronbach’s α = 0.79 to 0.96) [24]. *Safety* is defined as intervention-related adverse events. Safety will be assessed through study records by trainers and participants. *Perceived fit and recommendations* will be further assessed by quantitative survey data and open questions to allow more in-depth information on participants´ experiences with the *LAGOM* program. This will include the following items:The time required to participate in the *LAGOM* program was compatible with my daily work routine (five-point response scale, 1 = *totally disagree* to 5 = *totally agree*).The following course time was most compatible with my daily work routine: (drop-down menu of answers)The group size was appropriate (five-point response scale, 1 = *totally disagree* to 5 = *totally agree*).Would you recommend the *LAGOM* program to other employees? (yes/no and open field for reason)Would you recommend the trainer to other employees? (yes/no and open field for reason)What was particularly helpful about the *LAGOM* program? (open question)What would you recommend changing about the *LAGOM* program? (open question)

### Exploratory effectiveness evaluation

Since this is a feasibility study without sample size calculation, effectiveness measurements are made purely exploratory to evaluate the feasibility of questionnaires and assessment approaches. Like the development of the *LAGOM* program, the effect evaluation will be based on the IMA, which is why a consideration of the four main components in IMA (quality of life, behavior, environmental conditions, and determinants) is planned [14]. *Quality of Life*: Burnout symptoms will be assessed by the Maslach Burnout Inventory, the German version. The MBI addresses three subscales (Emotional Exhaustion [EE], Depersonalization [DP], and Personal Accomplishment [PA]) with 22 items that can be rated on a scale ranging from 0 = never to 6 = every day with higher scores indicating a higher level of burnout for EE and DP and lower scores indicating a higher level of burnout for PA. Validity and reliability of the MBI have been demonstrated to be good or acceptable (Cronbach´s α > 0.7 for all subscales) [25–27]. *Behavior*: changes in frequency and duration of taking breaks will be assessed daily through a diary, documented by participants throughout the program period. *Environmental conditions*: implementation of open ear appointments (whether they have taken place or not) will be assessed as an indicator of the environmental determinant. Information will be gathered by the research staff from participants via email or phone call. *Determinants*: occupational self-efficacy will be assessed by the BSW-5-Rev (German: Skala zur Messung der beruflichen Selbstwirksamkeitserwartung; scale for measuring work-related self-efficacy) [28]. It consists of 5 items that can be rated on a scale ranging from 1 = *completely disagree* to 4 = *completely agree,* indicating how far the statement applies to oneself or not. Research has shown good construct and criterion validity and acceptable internal consistency (Cronbach’s α = 0.73 for the employee version) [28].

### Semi-structured interviews

Semi-structured interviews will be conducted with three to six intervention participants to further explore their experience with the intervention. They will be selected strategically to represent a wide range of experience from the two disciplines, hospital units, and study sites. Questions selected for the interview will be based on understanding the complexity of experience, and topics that may have sensitive content or that arise from the questionnaires or course content. The interviews will be based on the following questions:What difficulties or obstacles did you experience in participating in the training?How did you perceive the support from your supervisor(s)? What did you feel supported by? What did you not feel supported by?How did participation in the training impact you personally?How was your participation perceived by your colleagues?Is there something that you would find helpful now that you have completed the training?What other ideas for the program do you have to promote a healthy working atmosphere?Finally, would you like to give us some advice for the finalization of the program?

Some results of the survey data may require an in-depth follow-up making additional interview questions necessary that cannot be stated a priori but are rather generated by survey data.

### Electrophysiological measures

The investigation of electrophysiological measures from which the autonomic regulation and the sympathovagal balance can be derived is a suitable method to evaluate the progress of the individual physical (stress-) state or the effect of a balancing and resilience-strengthening intervention [17, 29–31]. The electrophysiological recordings will be conducted at baseline and after the end of the intervention using a Somnomedics SOMNO HD electrophysiological measure recording system.

Electrophysiological measures will be derived from at least ten intervention participants at each study site. The main focus is to test whether the procedures of conducting electrophysiological recordings are feasible within a future trial rather than collecting complete data. Participants can sign up independently in a booking list with predefined appointments. The measurements are carried out by trained specialist staff in a quiet room on the clinic campus. A maximum of up to 30 min is planned for one measurement appointment. After a welcome and brief explanation of the procedure, the non-invasive measurement equipment is applied to the study participant, who is asked to sit quietly and move as little as possible during the recording. Movements and talking would otherwise impair the quality of the recorded signals and make post-processing even more necessary or completely unusable. The recording should provide at least 15 min of high-quality signals in a continuous session.

The feasibility of the electrophysiological measure analysis will be assessed at baseline by the following questions that can be rated on a five-point response scale ranging from 1 = *totally disagree* to 5 = *totally agree*:The time required for the electrophysiological measures was compatible with my daily work routine.The arrangement of the appointment for the electrophysiological measures was easy to make.The location for the electrophysiological measures was easy to find.

The following electrophysiological measures will be derived both at baseline and post-intervention in a resting seated position:Common electrophysiological measures monitoring device: electrocardiography (3-channel ECG), respiration activity (respiration-belt), pulse wave (finger clip PPG/photoplethysmography), and electrodermal activity (EDA, finger clips).Wearable (bracelet): pulse (heart rate), pulse wave (PPG), derivative respiration activity, and EDA.

The ECG records the heart’s activity and enables the time of each heartbeat to be registered. In order to analyze HRV, the times between the registered heartbeats are plotted in a tachogram (time series of all RR / beat-to-beat intervals, usually expressed in milliseconds). This RR series is then corrected for technical or physiological disturbances using different signal processing methods (such as filtering and artifact correction), resulting in an NN series (normal-to-normal time series). On the basis of this NN series, numerous HRV parameters can then be determined. The blood volume pulse derived from a photoplethysmography fingerclip (also used for pulse oximetry) allows for the registration of blood volume changes in the small vessels of the fingertip. This method also offers the possibility of registering heartbeats and calculating their beat-to-beat time intervals. HRV analyses are therefore also possible in this way in order to obtain cardiac information on the condition of the autonomic nervous system (ANS). However, vascular information can also be derived from the amplitude changes of this pulse wave signal, which provides additional information on the ANS status. The respiration belt adds another dimension to the ANS functioning. By stretching and compressing the belt during inhalation and exhalation, the breathing activity can be determined. This provides information about the duration and depth of the inspiration and expiration as well as the breathing rate. Finally, the measurement of the EDA yields information about the skin conductance (on the hands), which is sensitive to sweat. This gives a further dimension for estimating the ANS and can also serve as a stress marker. The measurements are also accompanied by simplified derivations using wearables. This is primarily intended to test the handling of these devices. In addition, it should then be possible to check internally whether these mobile devices alone would be qualitatively sufficient for evaluations in the future. These results may not be reported.

The selected electrophysiological measures are representatives of the state of autonomic regulation. In the feasibility study, the focus will be on the implementation and process for data collection of the electrophysiological measures. Since this is the main concern of this feasibility study, only two example HRV indices measures will be calculated from the recorded data. Based on these, the general calculation procedure of all future variability measures will be verified. The two standard HRV measures involved here are SDNN and RMSSD. SDNN is defined as the standard deviation of all NN (normal-to-normal heartbeat) intervals as a measure for total HRV while RMSSD as the square root of the mean squared differences of successive NN intervals reflects the short-term HRV. These are exemplary of a comprehensive assessment of the intervention effect on autonomic regulation in the following RCT. This future investigation will include numerous indices from HRV (cardiac activity function from ECG or PPG heartbeats), pulse wave variability (PWV, vascular variability function from PPG), EDA, and respiratory activity using different methods of electrophysiological measure analysis in time and frequency domains as well as non-linear dynamics.

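### SDNN and RMSSD can verify the heartbeat chain and time-domain HRV, but not the calculation procedure of all future variability measures

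*Protocol article*

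**What the plan says.** The relevant text is in the protocol article, Methods, Electrophysiological measures.

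- **Recorded:** ECG, respiration belt, finger-clip pulse wave (PPG) and EDA, at baseline and after the intervention, plus a wearable.
- **Calculated:** "only two example HRV indices measures will be calculated from the recorded data". They are defined there: "SDNN is defined as the standard deviation of all NN (normal-to-normal heartbeat) intervals", and "RMSSD as the square root of the mean squared differences of successive NN intervals".
- **Claimed:** "Based on these, the general calculation procedure of all future variability measures will be verified".
- **Planned for the RCT:** indices from HRV and from "pulse wave variability (PWV, vascular variability function from PPG), EDA, and respiratory activity", analysed in the time domain, in the frequency domain and by non-linear methods.

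The Outcome measures section adds that the electrophysiological analyses intended for the RCT are to be piloted in this study. Table 3 and the Quantitative part of Data analysis name no derived index other than SDNN and RMSSD.

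**The concern.** The section promises a result that its own calculation cannot produce. An index can only test the processing steps it passes through. SDNN and RMSSD pass through the heartbeat chain and end in two simple summary statistics. Several steps planned for the RCT lie outside that path.

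What is at stake is the conclusion the pilot may draw. If both indices compute without trouble, the sentence as written allows the report to say that the calculation of all later variability measures has been checked. For spectral HRV, non-linear HRV and pulse-amplitude variability, the pilot would hold no evidence from a calculated index.

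**Working it through.** The plan gives no figure to reproduce here. The check sets the definitions beside the list of RCT measures and is followed by one illustration.

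**Step 1: what the two indices use.** The section describes this chain: register heartbeats, form the RR series, correct it for disturbances, obtain the NN series. SDNN and RMSSD are then computed from the NN values alone:

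- SDNN = standard deviation of the NN intervals
- RMSSD = square root of the mean of (NN at i+1 minus NN at i) squared

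Neither formula contains skin conductance, belt signal, pulse amplitude, a spectral estimate or a non-linear statistic.

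**Step 2: comparison with the RCT list.**

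| Planned for the RCT | Exercised by SDNN and RMSSD? |
|---|---|
| Beat detection, artefact correction, NN series | Yes |
| HRV, time domain | Yes |
| HRV, frequency domain | Only up to the NN series |
| HRV, non-linear | Only up to the NN series |
| Pulse wave variability (vascular) | No. The section takes vascular information from pulse amplitude |
| EDA | No |
| Respiratory activity | No |

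**Step 3: count.**

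- Method domains within HRV: 1 of 3 (time; not frequency or non-linear).
- Signal families, if variability measures means HRV and pulse wave variability only: 1 of 2.
- Signal families, if it means the whole RCT list: 1 of 4.

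**Step 4: illustration on assumed data.** A 15-minute NN series was simulated with mean 850 ms, a 30 ms sine at 0.10 Hz, a 25 ms sine at 0.25 Hz and random noise with SD 10 ms. As a check, the expected SDNN is √(30²/2 + 25²/2 + 10²) = √862.5 = 29.4 ms, which matches the simulated value. The series was resampled at 4 Hz. The sampling rate was then misstated in the spectral step only. LF is 0.04–0.15 Hz and HF is 0.15–0.40 Hz.

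| Rate used in spectral step | SDNN (ms) | RMSSD (ms) | LF (ms²) | HF (ms²) | LF/HF |
|---|---|---|---|---|---|
| 4 Hz (correct) | 29.4 | 28.2 | 495 | 342 | 1.45 |
| 2 Hz (half) | 29.4 | 28.2 | 814 | 39 | 20.69 |
| 8 Hz (double) | 29.4 | 28.2 | 8 | 497 | 0.02 |

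Halving the rate moves the 0.25 Hz component to 0.125 Hz, into the LF band. Doubling it moves the 0.10 Hz component to 0.20 Hz, into the HF band, and the 0.25 Hz component to 0.50 Hz, outside both. SDNN and RMSSD do not change, because they are computed before the step that contains the error. The figures depend on the assumed series and the inserted error. The invariance does not.

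**The case against.** The case on the other side has real weight.

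- **Scope is disclosed.** The section says twice that the main concern is whether recordings can be carried out, and gives this as the reason for calculating only two indices. This stands. It justifies a short list of indices, but not the claim that the short list verifies all later measures.
- **The wording is softer than it first looks.** The sentence speaks of a *general* procedure and calls the indices *examples*. Frequency-domain and non-linear HRV start from the same NN series, so the shared stage is tested. This stands too, and the point is limited accordingly. The later estimation steps remain untested.
- **EDA and respiration may lie outside the claim.** The RCT list attaches the word variability to HRV and the pulse wave, not to EDA or respiration. The text does not settle this, so the point does not depend on it. Pulse wave variability is inside the claim on either reading.
- **PPG may be the beat source.** The section allows heartbeats from ECG or PPG and does not say which is used for SDNN and RMSSD. PPG would exercise pulse detection, but still not amplitude processing.

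A reader might go further and infer that three of the four recorded channels are never processed. The documents do not support that. PPG could supply the beats, a high-quality continuous signal is the stated recording target, and an internal quality check of the wearables is foreseen. The absence of a planned index does not show that a channel goes unexamined.

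A reader might also infer that the RCT could start on an untested pipeline. That is not supported either. The transition rests on a stakeholder discussion using criteria in an additional file that is not shown. The raw signals are recorded, so further indices could be derived before the RCT.

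**Conclusion.** The point holds in a limited form. SDNN and RMSSD can verify the shared heartbeat chain and time-domain HRV calculation. They do not verify spectral or non-linear HRV steps or pulse-amplitude processing, nor EDA or respiratory processing if those are intended. The claim to cover all future variability measures is therefore too broad even on its narrow reading of HRV plus pulse wave variability, and it sits poorly with the statement that the planned RCT analyses are piloted here.

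This rests on the definitions in the protocol article and on no assumed figure; the simulation only illustrates it. The consequence is modest: an overstated inference in a secondary component of a feasibility study. Piloting the acquisition of all channels is unaffected. The change is worth making because it costs little and improves what the pilot can say about the RCT analyses.

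**What to change.** **Preferred.** From the signals already recorded, derive one example index for each signal and method family planned for the RCT: for instance one spectral and one non-linear HRV index, one pulse-amplitude index, one EDA index and one respiratory index. For each, report the number of recordings from which it could be derived. These counts are a feasibility result in their own right.

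The cost is extra processing in MATLAB, which the Data analysis section already names. With the minimum of 20 participants measured at two time points, that is 20 × 2 = 40 recordings if all attend both. No additional visit or measurement is needed.

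**Otherwise.** Restrict the sentence to what the two indices can show, namely construction of the NN series and calculation of time-domain HRV measures. State that the remaining RCT measures are piloted for recording only, and qualify the matching statement in Outcome measures. This costs a change of wording.

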### Data analysis

#### Quantitative

A CONSORT flowchart (Fig. 2) will provide information on the number of participants screened, enrolled, and analyzed. Reasons for dropout during the intervention will be recorded and reported. A table showing baseline demographic and clinical characteristics will be presented. Adverse events will be reported. Since no confirmatory hypotheses are to be tested within the present pilot study, all exploratory effectiveness outcomes are evaluated and presented purely descriptively using means, medians, standard deviations, minimum, maximum, and percentages as appropriate. The electrophysiological measure analysis will include calculations of two standard HRV measures (SDNN and RMSSD) from at least 20 participants. All analyses will be performed using the Statistical Package for Social Sciences software (IBM SPSS Statistics for Windows, release 29.0; IBM Corporation, Armonk, NY) and MathWorks MATLAB (MATLAB version: 9.13.0 (R2022b), Natick, MA: The MathWorks Inc.; 2022).

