### Outcome measures

Data will be collected before (week 0), during (week 1–9) and after the trial (week 10) to assess the acceptability and feasibility of the trial procedures and intervention content. Data will be assessed via SoSci Survey, a web application for online surveys, as well as semi-structured interviews. Data on SoSci is collected and pseudonymized so that an assignment of baseline questionnaires to post-questionnaires but no identification of individuals is possible. Also, the electrophysiological measure analyses planned for the RCT following the feasibility study will be piloted within this study. Table 3 outlines the schedule of enrollment, data collection, and outcome measures.

**Table 3 Tab3:** Feasibility evaluation plan for the *LAGOM* Program

			Study period			
	Measures	Sources	Pre-Intervention	Baseline	*LAGOM*- program	Post-Intervention
				Week 0	Week 1–9	Week 10
Enrollment						
Eligibility screen	Eligibility checklist	Participants	X			
Informed consent and assent		Participants	X			
Data collection						
Sociodemographics	Survey	Participants		X		
Acceptability and feasibility evaluation (*N* = 30)						
Trial procedures						
Recruitment	Study records	Research staff	X			
Attrition	Study records	Research staff			X	X
Completeness of data collection	Study records	Research staff		X		X
Assessment process	Survey	Participants				X
Protocol adherence	Protocol checklist	Trainers, Research staff			X	
Intervention adherence	Study records	Trainers			X	
Intervention content and structure						
Satisfaction	Q4TE	Participants				X
Utility	Q4TE	Participants				X
Knowledge	Q4TE	Participants				X
Application to practice	Q4TE	Participants				X
Organizational results: individual	Q4TE	Participants				X
Organizational results: global	Q4TE	Participants				X
Safety	Study records	Trainers Participants			X	X
Perceived fit and recommendations	Survey	Participants				X
Effectiveness evaluation (exploratory)^a^ (*N* = 30)						
Quality of life						
Burnout symptoms	Questionnaire (MBI)	Participants		X		X
Behavior						
Break habits	Diaries	Participants			X	
Environmental conditions						
Open ear appointment	Email/Phone Call	Participants			X	
Determinants						
Self-efficacy	Questionnaire (BSW-5-REV)	Participants		X		X
Semi-structured interviews (*n* = 3 to 6)						
Perceived barriers	Interviews	Participants				X
Perceived support by supervisor(s)	Interviews	Participants				X
Perceived support from colleagues	Interviews	Participants				X

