#### Sample size

Since this is a feasibility study for which it is not necessary to adequately power for statistical null hypothesis testing, no formal sample size calculation was made a priori [33]. A fixed number of *N* = 30 was chosen, based on practical considerations and recommendations for good practice in pilot studies [34]. For the second qualitative phase, a strategic sub-set of three to six participants will be chosen to explore a wide range of experiences from the two disciplines, hospital units, and study sites. A minimum number of *n* = 20 with at least 10 participants from each site was selected as appropriate for evaluation of the electrophysiological measure procedures. Depending on feedback and schedule management, attempts will be made to include more participants.

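### Programme and assessment acceptability are rated only at week 10, with no rating scheduled at withdrawal, so the views of early leavers may go unrecorded

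*Protocol article*

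**What the plan says.** The protocol article has two main objectives: the feasibility and acceptability of the trial procedures, and of the programme's content and structure (Background). The enrolment target is stated as "A fixed number of *N* = 30 was chosen, based on practical considerations and recommendations for good practice in pilot studies".

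Under Outcome measures the timing is "Data will be collected before (week 0), during (week 1–9) and after the trial (week 10"). Table 3 gives the detail. The participant survey on the assessment process, all six Q4TE subscales, and perceived fit and recommendations are each marked in the week 10 column and nowhere else. The section on intervention content and structure says what the Q4TE is for: "In order to evaluate intervention acceptability, usefulness, participants´ learning, implementation, and transfer, the Questionnaire for Professional Training Evaluation (Q4TE"). The only participant feasibility ratings placed elsewhere are those on the electrophysiological procedure, which are taken at baseline.

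For people who leave, the Trial procedures section records the dropout and, if the person agrees to give one, a reason. It also records completed surveys at each time point and sessions attended. Three to six participants are interviewed: "They will be selected strategically to represent a wide range of experience from the two disciplines, hospital units, and study sites".

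For analysis, the Quantitative section says that "all exploratory effectiveness outcomes are evaluated and presented purely descriptively using means, medians, standard deviations, minimum, maximum, and percentages as appropriate". It also promises a flowchart with numbers enrolled and analysed, and a report of dropout reasons.

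**The concern.** A participant who withdraws in, say, week 3 has no scheduled occasion to rate satisfaction, utility, fit or survey burden, or to say whether they would recommend the programme. The same holds for the items asking whether survey time and diary effort were compatible with daily work. Someone who left because of that burden is not shown as ever being asked about it.

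The other sources do not fill the gap. A voluntary reason for leaving is not a rating. Attendance and attrition count people but do not record their judgement. The interviews are few, completion status is not among the stated selection features, and one of the listed questions addresses the interviewee as someone who has finished the training.

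At stake is the reading of a main objective. The results feed the discussion of programme changes before the pragmatic trial, and the Background itself names poor tailoring and low participation as weaknesses of earlier interventions. Leavers are likely to be the most informative about both. Unlike an analysis rule, a rating that was never collected cannot be recovered by a later statistical analysis plan.

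**Working it through.** The plan has no figure of its own to reproduce: the Sample size section states that "no formal sample size calculation was made a priori", and no expected dropout is given. The check therefore shows how far week 10 ratings could differ from the whole enrolled group.

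**Inputs**
- Enrolled: N = 30 (Sample size).
- Q4TE items coded 0 to 10; recommendation answered yes or no (Intervention content and structure).
- Assumed: k = 3, 6 or 9 ratings missing at week 10, so d = k/30 = 0.1, 0.2 or 0.3.
- Assumed: respondents' Q4TE mean of 8, and a mean of 0, 4 or 6 that the missing would have given.

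**Recommendation, every respondent saying yes.** The worst case counts each missing answer as no: (30 − k)/30.

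**Q4TE.** Full-cohort mean = (1 − d) × 8 + d × m, where m is the mean of the missing.

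| Missing | Respondents | Worst-case recommend | Q4TE, m = 6 | Q4TE, m = 4 | Q4TE, m = 0 |
|---|---|---|---|---|---|
| 3 | 27 | 27/30 = 90% | 7.8 | 7.6 | 7.2 |
| 6 | 24 | 24/30 = 80% | 7.6 | 7.2 | 6.4 |
| 9 | 21 | 21/30 = 70% | 7.4 | 6.8 | 5.6 |

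For example, with 6 missing and m = 4: 0.8 × 8 + 0.2 × 4 = 6.4 + 0.8 = 7.2, against 8 among respondents.

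**Recommendation, not unanimous.** With 6 missing and 22 of 24 respondents saying yes, the respondent figure is 22/24 = 91.7% (exact 95% CI 73.0 to 99.0%). Over all 30, the answer lies between 22/30 = 73.3% (all missing would say no) and (22 + 6)/30 = 93.3% (all would say yes). The respondent figure sits close to the top of that range.

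**The case against.** The strongest reply is that the loss will not be hidden. Attrition, survey completeness, attendance, dropout reasons and numbers analysed are all to be reported, so a reader will see the ratings beside the number who left. That stands, and it rules out saying that dropout by itself would pass for satisfaction. It does not supply the missing opinions.

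Second, nothing says that people who stop attending will not be sent the week 10 survey, and nothing bars them from interview. That also stands. A participant who stops the sessions but stays in the study may still answer; the gap concerns mainly those who withdraw from the study or do not respond.

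Third, analysis sets and the handling of missing answers are commonly left to the analysis plan or full protocol, neither of which is shown. A reader might infer that the plan restricts its summaries to week 10 responders. The article does not say so, and the quoted analysis sentence covers effectiveness outcomes only.

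A reader might go further and infer that burnout (MBI) and self-efficacy (BSW-5-Rev) will be compared as unpaired week 0 and week 10 summaries, so that loss of the most exhausted would mimic improvement. The documents do not support this. The listed statistics apply equally well to change scores, and Outcome measures notes that "an assignment of baseline questionnaires to post-questionnaires but no identification of individuals is possible", which makes pairing possible. These outcomes also carry no test: "effectiveness measurements are made purely exploratory to evaluate the feasibility of questionnaires and assessment approaches". Stating that change is paired would be at most a clarification that the analysis plan may already contain.

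**Conclusion.** The point holds for the acceptability ratings and rests on the assessment schedule, not on the analysis text. These ratings are scheduled once, at week 10, and nothing in the article obtains them from people who withdraw earlier. If those people are less satisfied, the acceptability results will be too favourable.

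How much is unknown. The gaps of 0.4, 0.8 and 1.2 Q4TE points (8 minus 7.6, 7.2 and 6.8), and the worst-case 90%, 80% and 70%, follow from assumed numbers missing and assumed opinions of the missing. The direction of selection is also an assumption: if leavers were as satisfied as stayers, there would be no bias. Nor can it be checked which denominator the criteria for moving to the pragmatic trial use, because Additional file 1, Table S1 is not shown.

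This is an inexpensive improvement to a main objective, not a contradiction in the protocol. No finding is made against the burnout or self-efficacy analysis.

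**What to change.** 1. Add a withdrawal row to Table 3: a short, voluntary online form with the Q4TE satisfaction and utility items, the assessment-process items, perceived fit and recommendation. It must remain clear that nobody is obliged to answer or give a reason. Report these answers separately from the week 10 ratings, since they are given at a different point in the programme.
2. Beside each week 10 acceptability result, give the number responding out of all enrolled.
3. For recommendation, add a bound over all enrolled in which non-response counts as not recommending.

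The first item has to be in place before participants leave; the other two are reporting changes. The cost is a few voluntary minutes per leaver and a few extra table entries. The headline acceptability figures may also come out less favourable.
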